The SmArt-E trial is set up according to the Medical Research Council (MRC) framework for evaluating complex interventions and serves three objectives. The first aim is to evaluate the effectiveness of a blended care intervention in patients with hip and/or knee OA compared to usual care on health-related measures with physical functioning and pain at 12-month follow-up being defined as primary outcomes. As a second objective, we assess the cost-effectiveness and cost-utility of the intervention compared to usual care. Thirdly, using a mixed-methods design, a process evaluation of the blended care approach will reveal challenges and barriers related to its implementation that might affect the outcomes.

Primarily, it is hypothesized that the SmArt-E intervention would improve physical functioning and decrease pain more than usual care among patients with hip and/or knee OA. Moreover, we assume that the SmArt-E intervention will further increase quality of life, participation and PA, enhance empowerment, self-efficacy and coping skills, reduce risk factors for joint replacement surgery and retain work ability to a greater extent compared to usual care (secondary hypothesis).

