	Arm 2: control group: usual care
Key inclusion and exclusion criteria	Sex: All Minimum Age: 38 Years Maximum Age: no maximum age Additional Inclusion Criteria: Medically/physician-diagnosed osteoarthritis (ICD-10-GM: M.15 polyarthrosis, M16. - coxarthrosis, and M17. gonarthrosis) and fulfillment of the American College of Rheumatology criteria for knee/hip osteoarthritis. Age > 50 and > 38 years for hip and knee osteoarthritis, respectively.
	Exclusion of participants who have already had joint replacement of the affected index joint (total joint arthroplasty).
Study type	Interventional
Date of first enrolment	Nov, 2022
Target sample size	330
Recruitment status	Recruiting ongoing
Primary outcome(s)	#1a: Hip Disability and Osteoarthritis Outcome Score (HOOS) OR #1b: Knee Injury Osteoarthritis Outcome Score (KOOS) AND #2: Numeric Rating Scale (NRS) to assess pain severity

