#### Primary outcomes

The primary outcomes are physical functioning and pain. Physical functioning will be assessed using the subscale “function in daily living” of the Hip Disability and Osteoarthritis Outcome Score (HOOS) [40] or of the Knee injury and Osteoarthritis Outcome Score (KOOS) [41], depending on the index joint. Both questionnaires are validated in German language comprising 40 and 42 items, respectively, distributed across the five subscales pain, symptoms and function in daily living, sports activities and quality of life [40, 41]. Each item is scored on a five-point Likert scale (0 = extreme symptoms/problems; 4 = no symptoms/problems). Hence, lower scores indicate higher impairments. Pain will be assessed using an 11-item numeric rating scale (NRS) [42, 43]. Patients select a number (0–10 integers) that reflects their pain intensity best on a horizontal bar [43], ranging from zero (“no pain”) to ten (“worst pain imaginable”) and related to the previous 24 hours [42, 43].

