#### Sample size

We aim to recruit 330 patients, equally distributed among the intervention and control group. The sample size calculation assumes an effect size of Cohen’s *d* = 0.34 for the comparison of the *SmArt-E* intervention and usual care for the primary outcomes of pain and physical functioning after 12 months. This assumption is derived from a recent meta-analysis involving 44 clinical studies evaluating internationally established, comparable exercise therapy compared to *do-nothing* or *sham* control conditions and a dropout rate of 15%, resulting in effect sizes of *d* = 0.49 for pain and *d* = 0.52 for physical functioning [23]. A comparable RCT with digital support demonstrate similar results, in which the authors find a greater pain reduction of approximately − 1.0 (±2.3) points on a 11-point NRS in the intervention group compared with the control group, corresponding to an effect size of *d* = 0.44 [33]. Regarding physical functioning, an effect of *d* = 0.66 is observed. We assume smaller effect sizes for the SmArt-E intervention as this will be compared to current usual care, which should be more effective than *Do-Nothing* or *Sham*. Based on a *t*-test for independent samples, one-sided *α* = 0.05 and *β* = 0.80, a sample size of *n* = 274 is necessary when considering the number of outcomes and Bonferroni corrections (*n* = 137 per group). Target sample size is increased to *n* = 330 to compensate for dropouts of up to 20%. Additional power is gained by statistically accounting for age, gender, and the baseline value of the respective outcome.

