#### Statistical analysis

The primary outcomes comprising physical functioning (HOOS/KOOS) and pain reduction (NRS) at 12 months from baseline are compared between the intervention and control group using Bonferroni-adjusted analysis of covariance with gender, index joint, allocation (individual/group treatment), baseline values (pain and physical functioning) and the study centre as covariates. In sub-group analyses, corresponding models will be applied only to patients with hip or knee OA and only to women or men, respectively. Wherever required, differences in the effects are tested by expanding the overall model with corresponding interaction terms. Study centre effects are studied in a similar way. A secondary analysis will examine intervention group differences in the time course of pain and physical functioning, including all assessment appointments and using mixed models. Effects on the secondary outcomes are investigated descriptively (and without Bonferroni correction) using appropriate regression models. The analysis is primarily based on the *intention-to-treat* principle. Missing values will be considered by multiple imputation and *maximum likelihood* principle, respectively. If large numbers of imputations will be necessary, a robustness analysis with alternative imputation strategies will be carried out. All statistical analyses are defined in a Statistical Analysis Plan prior to the completion of patient recruitment.

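### Plain Bonferroni on the two 12-month primary outcomes is valid, but Holm's step-down version would give more power at the same family-wise limit and the same sample size

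*Protocol article*

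**What the plan says.** The protocol article names two primary outcomes (Primary outcomes): "The primary outcomes are physical functioning and pain". The Introduction gives a directional hypothesis on each: "it is hypothesized that the SmArt-E intervention would improve physical functioning and decrease pain more than usual care". Table 1 (Study design) lists HOOS or KOOS, then "AND #2: Numeric Rating Scale (NRS) to assess pain severity".

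Under Statistical analysis, the two outcomes at 12 months are compared between groups "using Bonferroni-adjusted analysis of covariance", with baseline values, gender, index joint, treatment allocation and centre as covariates. Under Sample size, the same effect, d = 0.34, is assumed for pain and for function. The calculation is a two-sample t-test with "one-sided *α* = 0.05 and *β* = 0.80, a sample size of *n* = 274 is necessary", and this number is reached "when considering the number of outcomes and Bonferroni corrections (*n* = 137 per group"). The same section expects additional power from adjusting for age, gender and the baseline value.

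The article names no step-down or hierarchical procedure and no rule that both outcomes must be significant. It says that a separate statistical analysis plan will define all analyses; that plan is not available here.

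**The concern.** Under single-step Bonferroni each outcome is tested at half the family level, whatever the other one shows. Once one of two hypotheses has been rejected, only one remains, and it can be tested at the full level without exceeding the family-wise limit. Holm's procedure does this and Bonferroni does not.

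The trial expects both outcomes to improve and assumes the same effect on each, which is the situation in which the second step helps most. What is at stake is some chance of confirming the second outcome once the first has been shown. The validity of the trial is not in question.

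**Working it through.** **Inputs.** From Sample size: d = 0.34 on both outcomes, one-sided family α = 0.05, power 0.80 (the article labels it β), 137 per group, 1:1 allocation ("We aim to recruit 330 patients, equally distributed among the intervention and control group"). Two assumptions are not in the documents: the correlation ρ between the two test statistics, taken from 0 to 0.9, and the share of outcome variance explained by the covariates, R².

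**Step 1: reproduce the plan's figure.** A noncentral-t calculation for d = 0.34 and power 0.80 gives:

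- one-sided 0.05, no correction: 108 per group, 216 in total;
- one-sided 0.05/2 = 0.025: 137 per group, 274 in total, power 0.8007;
- two-sided 0.025: 166 per group, 332 in total.

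Only 0.025 in one tail gives 274. (Two-sided 0.05 without correction is numerically the same test, but the text says one-sided with Bonferroni.) The sizing is therefore single-step α/2.

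**Step 2: power without covariate adjustment.** Normal approximation: δ = 0.34 × √(137/2) = 2.814, with critical values 1.960 (0.025) and 1.645 (0.05). Φ₂ is the bivariate normal distribution function with correlation ρ.

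- Bonferroni, per outcome: Φ(δ − 1.960) = Φ(0.854) = 0.803
- Bonferroni, both: B = Φ₂(δ − 1.960, δ − 1.960)
- Mixed term: M = Φ₂(δ − 1.960, δ − 1.645)
- Holm, both: 2M − B
- Holm, per outcome: 0.803 + M − B
- At least one outcome, either method: 2 × 0.803 − B

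At ρ = 0.5, B = 0.692 and M = 0.7415. Holm for both is 2 × 0.7415 − 0.692 = 0.791, and Holm per outcome is 0.803 + 0.7415 − 0.692 = 0.853.

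| ρ | Per outcome, Bonferroni → Holm | Both, Bonferroni → Holm | At least one, either method |
|---|---|---|---|
| 0 | 80.3% → 86.4% | 64.6% → 76.7% | 96.1% |
| 0.3 | 80.3% → 85.8% | 67.1% → 78.0% | 93.6% |
| 0.5 | 80.3% → 85.3% | 69.2% → 79.1% | 91.5% |
| 0.7 | 80.3% → 84.7% | 71.7% → 80.5% | 89.0% |
| 0.9 | 80.3% → 83.8% | 75.4% → 82.3% | 85.3% |

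**Step 3: power with covariate adjustment.** Covariates that explain a share R² of the variance raise the effective effect to 0.34/√(1 − R²), so δ becomes 2.814/√(1 − R²). At ρ = 0.5:

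| R² | δ | Per outcome, Bonferroni → Holm | Both, Bonferroni → Holm |
|---|---|---|---|
| 0.16 | 3.070 | 87% → 91% | 78% → 86% |
| 0.25 | 3.249 | 90% → 93% | 83% → 90% |
| 0.36 | 3.518 | 94% → 96% | 90% → 94% |

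The gain is about 2–4 points per outcome and 5–8 points for both.

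**Step 4: family-wise error.** If both null hypotheses are true, Holm errs only when the smaller p is at most 0.025, exactly as Bonferroni does: 0.0494 at ρ = 0, 0.0454 at ρ = 0.5 and 0.0352 at ρ = 0.9. If only one is true, a false claim needs that outcome's p to be at most 0.05, so the error is at most 0.05. With d = 0.34 on the other outcome it is 0.045 to 0.050, against 0.025 under Bonferroni. The guaranteed limit is the same, and Holm uses more of it.

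**The case against.** The strongest reply is that nothing here is wrong. Bonferroni is valid, fixed in advance, and used consistently in the sizing and the analysis. Splitting α lets each outcome carry its own claim, and for that purpose the planned 80% per outcome is met. All of this stands, and it limits the point to efficiency.

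A reader might infer from the hypothesis and from the AND in Table 1 that both outcomes must succeed, so that the trial's real power is only about 69%. The documents do not support this. The AND joins entries in a registry list and is not a decision rule. If both were required, each could be tested at the full 0.05 and no α split would be needed. The 69% also holds only at ρ = 0.5 and without the covariate adjustment that the article plans; with adjustment the corresponding figure is 78–90% under the assumed R².

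It would also be too strong to say that Holm costs nothing. If Bonferroni-level intervals are reported, an outcome with one-sided p between 0.025 and 0.05, rejected only at the second step, would be claimed while its interval includes no effect. Wanting tests and intervals to agree is a legitimate reason to keep Bonferroni.

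Finally, sizing on plain Bonferroni is compatible with a Holm analysis, and the unseen analysis plan may already specify one. The article itself says only Bonferroni.

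**Conclusion.** The point holds as a cheap improvement to a valid method. At every correlation and R² examined, Holm is at least as good for each outcome and keeps the family-wise limit without an independence assumption. Without covariate adjustment the gain is about 3.5 to 6 points per outcome and 7 to 12 points for showing both; with adjustment it is smaller but still positive. There is no gain for showing at least one outcome.

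The size rests on the planned d = 0.34 holding for both outcomes, on 137 evaluable patients per group, and on assumed values of ρ and R². The direction does not depend on them. The documents do not support calling the Bonferroni choice an error, or calling the trial underpowered because of it.

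**What to change.** Before any outcome data are seen, state in the protocol and the analysis plan that the two 12-month primary outcomes are tested by Bonferroni-Holm: the smaller p-value at one-sided 0.025 and, only if that is rejected, the other at one-sided 0.05. State that a claim is made for each outcome rejected. Leave the sample size as it is.

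State which intervals will be reported. If they stay at the Bonferroni level, add a sentence that an outcome rejected only at the second step will have an interval that includes no effect, and how this will be presented. The cost is a few sentences and that mismatch; no patients or data are added.

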4. What: Procedures	The SmArt-E intervention is divided into an in-person phase and a self-training phase. If more than four persons are interested in participating at the same time, the intervention can take place in a group setting, otherwise it is conducted in individual physiotherapy sessions. Each session consists of an educational and exercise part. The first session is also about getting to know the app and its functions. During the self-training phase, the participants continue the intervention with the support of the mobile phone app. In case of questions or problems, it is possible to contact the physiotherapist via the chat function of the app. Six months after the start of the intervention, refresher sessions will take place to repeat specific educational content. If necessary, additional individual physiotherapy can be delivered.
5. Who provided	Trained physiotherapists perform the in-person exercise programme and education as well as the refresher sessions. Physiotherapists receive 2 days (4 hours each) of training specific to the SmArt-E intervention from skilled members of the study team. Individual therapy (if required) can be delivered by any physiotherapists without special training.
6. How	During the in-person phase, the intervention is provided in either individual (one-to-one) or group setting (4–8 participants). After the in-person phase, SmArt-E also includes the phase of self-training planned from the distance with the support of a mobile phone app and with remote physiotherapeutic support using the app’s chat feature.
7. Where	Three study centres: Bochum/Dortmund/Essen (North Rhine-Westphalia, Germany), Cottbus/Senftenberg (Brandenburg, Germany), Tübingen/Reutlingen (Baden-Württemberg, Germany) The in-person sessions are delivered in an outpatient physiotherapy setting. During the self-training phase, participants decide themselves where to exercise, probably in their own homes. Individual physiotherapy and refresher sessions will also take place in the respective physiotherapy practice.

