### Usual care

The control group receives usual care, which might comprise physiotherapy sessions, but also other treatments like injections, acupuncture, or no treatment at all. An additional 45-minute consultation with a physiotherapist on PA-recommendations for OA including informational material, access to the app, and a smartphone if sought, is offered following the final assessment.

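### The primary ANCOVA adjusts for individual or group delivery, a non-randomised feature of SmArt-E that controls do not have; under ordinary codings the arm term is inestimable, loses the controls, or shifts to one delivery mode versus usual care

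*Protocol article*

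**What the plan says.** The Statistical analysis section states that the two primary outcomes at 12 months "are compared between the intervention and control group using Bonferroni-adjusted analysis of covariance". The covariates it names are those of a "Bonferroni-adjusted analysis of covariance with gender, index joint, allocation (individual/group treatment), baseline values (pain and physical functioning) and the study centre as covariates". The same paragraph says: "The analysis is primarily based on the *intention-to-treat* principle".

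Individual and group are described throughout as the two ways of delivering SmArt-E (Table 1, Table 2, and the intervention summary). Table 3, item 6, says: "During the in-person phase, the intervention is provided in either individual (one-to-one) or group setting (4–8 participants". Item 4 gives the rule for choosing between them: "If more than four persons are interested in participating at the same time, the intervention can take place in a group setting"; otherwise sessions are individual.

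For the other arm, the Usual care section says: "The control group receives usual care, which might comprise physiotherapy sessions, but also other treatments like injections, acupuncture, or no treatment at all". No section gives controls a value on delivery mode.

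Under Randomization and blinding, allocation takes place at the initial assessment with index joint, sex and centre as strata. Delivery mode is not a stratum, and only intervention participants are directed to a participating practice.

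**The concern.** A covariate in a between-arm ANCOVA should be defined in both arms and be unaffected by allocation. Delivery mode is part of the experimental treatment, so it has no counterpart among controls. Its value depends on local numbers, not on randomisation.

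What is at stake is the meaning of the main result for both primary outcomes. The objective is SmArt-E as a whole against usual care. With mode in the model, the arm coefficient can become a comparison of all controls with only those intervention participants treated in one mode. That subset was not formed by randomisation. Participants in areas where enough people came forward at once may differ in prognosis from the others, and the comparison would carry that difference.

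The protocol's own figures make it unsafe to presume that the two modes work equally well. The intervention summary gives group delivery 12 × 80 = 960 minutes in person and individual delivery 4–8 × 40 = 160–320 minutes, a three- to six-fold difference. Table 1 gives 6–8 individual appointments (240–320 minutes), which is still three- to four-fold. The two session counts need reconciling, but that is a separate matter.

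**Working it through.** **Inputs from the Sample size section:** d = 0.34; one-sided α = 0.05 with Bonferroni correction over two outcomes, so 0.025 each; power 0.80 (printed as β); 137 per group.

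**Inputs assumed, because the protocol does not give them:** the share treated in groups, the effect in each mode, and a baseline–outcome correlation of 0.5 where stated.

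**Step 1: reproduce the planned sample size.** n per group = 2(1.960 + 0.842)²/0.34² = 135.8, so 136. The exact noncentral t gives 137 per group (274 in total) with power 0.801. The stated 274 reproduces.

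**Step 2: what the arm coefficient means.** Write C, I and G for the mean outcomes of controls, individual delivery and group delivery, and fit intercept, arm and mode.
- *Control/individual/group factor alongside arm:* intercept, arm and the two mode indicators make four columns of rank 3. No separate arm effect exists.
- *Controls missing on mode:* they leave the model, or the planned multiple imputation gives them a delivery mode that they never had.
- *Controls coded as individual:* the arm coefficient is I − C.
- *Controls coded as group:* the arm coefficient is G − C.

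**Step 3: precision when controls are coded to one mode.** Take controls coded as individual, with n_I = 137 × (1 − group share). The ratio of standard errors with and without mode is √[(1/n_I + 1/137)/(2/137)]. Without mode, d/SE = 0.34/√(2/137) = 2.814, and power = Φ(2.814 − 1.960) = 0.80. With mode, power = Φ(2.814/ratio − 1.960).

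| Assumed share in groups | n_I | SE ratio | Power |
|---|---|---|---|
| 30% | 95.9 | 1.10 | 0.72 |
| 50% | 68.5 | 1.22 | 0.63 |
| 70% | 41.1 | 1.47 | 0.48 |

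These assume d = 0.34 in both modes and no gain from the baseline value. If controls are coded as group, the 30% and 70% rows change places.

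**Step 4: allow for the baseline covariate.** With correlation 0.5 the residual SD is √0.75 = 0.866, so d/SE = 2.814/0.866 = 3.25 and power is 0.90. With mode added and half in groups, 3.25/1.22 = 2.65 and power is 0.76. Simulation (2,000 runs per scenario) agreed: about 0.90–0.91 without mode and 0.76–0.77 with it.

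**Step 5: unequal modes.** Assume 0.24 for individual and 0.44 for group, half in each, so the overall effect is 0.5 × 0.24 + 0.5 × 0.44 = 0.34. In simulation with baseline correlation 0.5:

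| Model | Mean arm estimate | Power |
|---|---|---|
| No mode term | 0.34 | 0.89 |
| Mode, controls coded individual | 0.24 | 0.46 |
| Mode, controls coded group | 0.44 | 0.93 |

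The same trial gives two different answers depending on a code that has no meaning for controls.

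**The case against.** The strongest reply is that the damage depends on coding, and that coding is a detail an article may leave to the analysis plan. Part of this stands. A reader might infer that no coding can work, and that is not so. If mode is centred within the intervention arm and controls are set to 0, the mode column sums to zero in that arm. It is then orthogonal to intercept and arm, so the arm coefficient is again the overall difference with essentially no loss of power. A three-level factor that replaces arm, with a weighted contrast of the two modes against control, also recovers it. But the protocol specifies neither, and the covariate itself is already fixed in the published primary model.

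Three further readings are tempting and go beyond the documents.
- *That mode is set after randomisation.* Table 3 gives a rule but no time point. Late setting is a reasonable inference, because mode concerns only those treated at a practice and is not a stratum. The point does not depend on it: a variable undefined in one arm is unsuitable either way.
- *That the model contradicts intention-to-treat.* It moves nobody between arms. Only exclusion of controls with missing mode would remove randomised participants, and the protocol does not propose that.
- *That the arm term must be biased.* If the modes have equal effects and mode is unrelated to prognosis, the coefficient keeps its expected value and only precision is lost.

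The 72/63/48% figures also leave out the gain from covariate adjustment that the Sample size section expects. With that gain, the loss starts from a higher level, as Step 4 shows.

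Usual care may include physiotherapy, so one might try to give controls a mode of their own. The protocol does not do so, and controls with no treatment would still have no value.

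**Conclusion.** The point holds: the primary model as written includes a covariate that does not belong in it. Entered in the ordinary ways, delivery mode leaves the arm effect inestimable, loses or imputes the controls, or replaces SmArt-E versus usual care with a non-randomised part of it.

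The size is conditional. The power losses in Steps 3 and 4 apply only when controls are coded to one mode, and they rest on assumed group shares and, in Step 4, an assumed correlation. The shift from 0.34 to 0.24 or 0.44 also rests on assumed mode effects. None of these figures predicts what this trial will show. They show that the primary result would hang on an unstated coding decision, while the large difference in contact time makes equal mode effects an unsafe assumption.

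**What to change.** Delete the individual/group treatment term from the primary ANCOVA. Keep arm, the stratification factors (index joint, sex, centre) and the baseline values. Examine delivery mode only as an exploratory comparison within the intervention arm, labelled as non-randomised.

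The cost is wording in the protocol and analysis plan. Sample size, data collection and conduct do not change. The protocol has the analysis plan defined before recruitment is complete, which is the natural point to make the correction.

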## Abstract

**Introduction:**

Hip and knee osteoarthritis are associated with functional limitations, pain and restrictions in quality of life and the ability to work. Furthermore, with growing prevalence, osteoarthritis is increasingly causing (in)direct costs. Guidelines recommend exercise therapy and education as primary treatment strategies. Available options for treatment based on physical activity promotion and lifestyle change are often insufficiently provided and used. In addition, the quality of current exercise programmes often does not meet the changing care needs of older people with comorbidities and exercise adherence is a challenge beyond personal physiotherapy. The main objective of this study is to investigate the short- and long-term (cost-)effectiveness of the SmArt-E programme in people with hip and/or knee osteoarthritis in terms of pain and physical functioning compared to usual care.

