**Methods:**

This study is designed as a multicentre randomized controlled trial with a target sample size of 330 patients. The intervention is based on the e-Exercise intervention from the Netherlands, consists of a training and education programme and is conducted as a blended care intervention over 12 months. We use an app to support independent training and the development of self-management skills. The primary and secondary hypotheses are that participants in the SmArt-E intervention will have less pain (numerical rating scale) and better physical functioning (Hip Disability and Osteoarthritis Outcome Score, Knee Injury and Osteoarthritis Outcome Score) compared to participants in the usual care group after 12 and 3 months. Other secondary outcomes are based on domains of the Osteoarthritis Research Society International (OARSI). The study will be accompanied by a process evaluation.

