Key secondary outcomes	Three assessments are scheduled: 1. T0 assessment = following enrolment and before randomization/ start of the intervention; 2. T1 assessment = 3 months after the start of the intervention/ after completion of the in-person intervention; 3. T2 = after completion of the 12-months study period. 1. HOOS or KOOS and NRS after 3 months 2. Physical performance tests (modified Y-Balance Test; 30-second Sit-to-Stand Test) after 3 and 12 months 3. Daily physical activities (assessment is device-based and questionnaire-based) after 3 and 12 months Questionnaire surveys: 4. Action and coping planning (Action Planning & Coping Planning) at 3 and 12 months. 5. Quality of life/ health status (European Quality of Life 5 Dimensions 5 Level Version (EQ-5D-5L), Patient Global Assessment (PGA) and self-rated change in health status after 3 and 12 months 6. Assessment of coping strategies for pain and its evaluation (Pain Catastrophizing Scale, PCS) after 3 and 12 months 7. Self-report behavioural automaticity index (SRBAI) after 3 and 12 months 8. Assessment of the general improvement of the disease (Patient Acceptable Symptom Scale, PASS) after 3 and 12 months 9. Self-efficacy/ empowerment (Arthritis Self-Efficacy Scale, ASES) after 3 and 12 months 10. Patient satisfaction (ZUF-8) and an additional item assessing the patient’s perspective on the satisfaction with the results of the treatment after 3 and 12 months 11. Physical activity health competence (short form) after 12 months 12. Usability: System Usability Scale (SUS) after 3 months and mHealth App Usability Questionnaire (MAUQ) after 12 months 13. Questions on health care expenditures (financial expenditures due to osteoarthritis-related knee/hip problems for utilization of health care providers, therapeutic treatments, aids, etc.) for the period 12 months before study inclusion and during the 12-months intervention period

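### The 3-month pain and function effects are a stated secondary hypothesis but are left descriptive; testing each one after its own 12-month result would allow a confirmatory claim at no cost in alpha, power or patients

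*Protocol article*

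**What the plan says.** The abstract's Introduction opens the objective with "The main objective of this study is to investigate the short- and long-term (cost-)effectiveness of the SmArt-E programme" and ties it to pain and physical functioning. The abstract's Methods paragraph continues: "The primary and secondary hypotheses are that participants in the SmArt-E intervention will have less pain (numerical rating scale) and better physical functioning", compared with usual care, at 12 and at 3 months. Read in order, 12 months is the primary hypothesis and 3 months the secondary one. In Table 1 (Study design), the first key secondary outcome is "HOOS or KOOS and NRS after 3 months".

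The Statistical analysis section gives Bonferroni-adjusted analysis of covariance to the two 12-month outcomes only. Two other sentences there reach the 3-month data. One concerns the time course: "A secondary analysis will examine intervention group differences in the time course of pain and physical functioning, including all assessment appointments", using mixed models. The other covers secondary outcomes in general: "Effects on the secondary outcomes are investigated descriptively (and without Bonferroni correction) using appropriate regression models". The section assigns no significance level to the time-course model and states no testing order for the 3-month effects.

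**The concern.** A directional hypothesis on the trial's two main outcomes has no test that could confirm it. Both 12-month tests may succeed and the 3-month estimates may be clear, yet the trial could still only describe the early effect.

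The 3-month visit has a meaning of its own. Table 1 places it after completion of the in-person phase, and the Introduction notes that exercise effects in this condition may be only short-term. Controlled statements at both time points would show that an early benefit was present and that it lasted.

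The protocol defers detail to a statistical analysis plan that is not shown. However, the descriptive status of secondary outcomes is fixed in the protocol itself.

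**Working it through.** **Inputs from the Sample size section.** The test settings are "one-sided *α* = 0.05 and *β* = 0.80"; the second figure is read as power 0.80, the only reading that fits. The stated n "is necessary when considering the number of outcomes and Bonferroni corrections"; with two primary outcomes this means 0.05/2 = 0.025 one-sided each. The effect: "The sample size calculation assumes an effect size of Cohen’s *d* = 0.34" at 12 months. The stated result is 274 evaluable patients, 137 per group.

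**Step 1: the plan's own figure.** Normal approximation: n per group = 2(1.960 + 0.842)² / 0.34² = 2 × 7.85 / 0.1156 ≈ 135.8, so 136. The exact two-sample t-test gives 136.8, so 137 per group and 274 in total, with power 0.801. The stated figure is reproduced.

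**Step 2: error control with an ordered test.** Take two sequences, 12-month pain then 3-month pain, and 12-month function then 3-month function. Each step is tested at one-sided 0.025, and the second step only if the first rejects. Within one sequence:

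- If the 12-month null is true, any false claim must begin with its rejection, so the probability is at most 0.025.
- If the 12-month null is false and the 3-month null is true, a false claim needs rejection at 3 months, so the probability is again at most 0.025.

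Over both sequences the total is at most 0.025 + 0.025 = 0.05. A simulation of 1,000,000 runs per scenario, over five null/alternative configurations and four correlation settings, gave 0.0435 to 0.0500.

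Without an order, and with independent tests, four tests at 0.025 give 1 - 0.975⁴ = 0.096. Keeping 0.025 at 12 months and using 0.05 at 3 months gives 1 - 0.975² × 0.95² = 0.142. The order is what makes the extra claims legitimate.

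**Step 3: what is gained.** The protocol gives no 3-month effect size and no correlation between time points, so both are assumed. With 137 per group the test statistic has mean d × √(137/2) = 8.28d. At 12 months this is 2.81, and power is Φ(2.81 - 1.96) = 0.80. The table uses d = 0.34 at 12 months, correlation 0.3 to 0.7 between the two time points and 0.5 between pain and function.

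| Assumed 3-month d | 3-month power taken alone | Confirmed at 12 and 3 months, given outcome | Confirmed at 3 months, at least one outcome |
|---|---|---|---|
| 0.20 | 0.38 | 0.34-0.37 | 0.49-0.53 |
| 0.34 | 0.80 | 0.67-0.72 | 0.83-0.86 |
| 0.44 | 0.95 | 0.78-0.79 | 0.90-0.91 |

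As a check, each entry in the third column must lie between the product of the two powers (zero correlation) and the smaller of them. For d = 0.34 these are 0.803 × 0.803 = 0.645 and 0.803, and 0.67-0.72 lies between.

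**Step 4: sensitivity to dropout.** With 330 recruited and 20% lost, 330 × 0.80 / 2 = 132 per group remain. The third column becomes 0.32-0.36, 0.65-0.70 and 0.76-0.78. The conclusion does not depend on which of the two sample sizes is reached.

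**The case against.** The strongest reply is that nothing here is wrong. Primary outcomes get error control and secondary outcomes do not, and the protocol says so openly. A secondary hypothesis need not be confirmatory. This stands: the point is a missed gain and a mismatch with the abstract's framing, not an invalid test.

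Three further replies also have weight.

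- The gain is conditional. If a benefit is present at 3 months and lost by 12, the proposed order yields no confirmatory claim in just the case where the early result would be most interesting.
- A reader might infer that half of the main objective goes unexamined. The documents do not support that. The short-term element of the objective comes from the abstract. The Introduction of the article names 12-month pain and function as primary, and its own secondary hypothesis lists other outcomes. Month 3 is also covered by the planned time-course model, although without a place in the error control.
- A reader might infer that the mixed model treats baseline as an unconstrained response, so that the 3-month estimate loses precision. The Statistical analysis section does not say how baseline enters that model. The regression models promised for secondary outcomes may well be baseline-adjusted, and such parametrisation properly belongs to the unseen analysis plan. No loss of precision can be charged to the protocol.

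**Conclusion.** The point holds as an improvement at no cost. As written, the protocol excludes a confirmatory 3-month statement on pain or function in every scenario. A fixed order within each outcome would permit one with family-wise error still at or below one-sided 0.05. The error bound holds for any correlation. The size of the gain does not come from the protocol: it rests on assumed 3-month effects and correlations, and ranges from about one chance in three per outcome at d = 0.20 to nearly four in five at d = 0.44. It also assumes that the planned d = 0.34 is true at 12 months. The descriptive analysis remains permissible if the trial team prefers it, but the abstract's 3-month hypothesis should then be read as non-confirmatory.

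**What to change.** Add one rule to the Statistical analysis section or to the statistical analysis plan, before any unblinded data are seen: *For each primary outcome, if the 12-month null hypothesis is rejected at its Bonferroni-adjusted level, the 3-month null hypothesis for the same outcome is tested at that level with the same baseline-adjusted model; otherwise the 3-month result is descriptive.* The sentence on secondary outcomes should then exempt these two tests.

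The cost is that wording. The 12-month tests, their levels, their power and the 274 evaluable patients are unchanged. An outcome that fails at 12 months is reported at 3 months exactly as it would be now. The protocol already schedules the analysis plan to be completed before recruitment ends, so the rule fits the existing timetable.
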